### Vascular health evaluation

#### Endothelial function by peripheral arterial tonometry (PAT)

Non-invasive peripheral endothelial function will be assessed by reactive hyperemia index (RHI) using Endo PAT 2000 Machine (Itamar Medical Ltd, Caesarea, Israel). Endothelial function test will be administrated by a trained staff in a separate room and performed in the morning or early afternoon (starting time between 7:30 AM and 11:00 AM). The Endo-PAT data will be analyzed with the proprietary software package, without any input from the examiner and has been developed to measure observer independent pulsatile arterial volume changes by finger plethysmography. The temperature of the testing environment is 22–25 °C, dim the lights and keep quiet. The required equipment includes a comfortable examination bed, a computer, Endo-PAT equipment, hand support, and a blood flow occlusion meter. The test takes a total of 16 min, including baseline 6 min, interruption of 5 min, and release of 5 min. The subject takes a supine position, relax, and his arms can be placed flat on both sides of the body. Subjects avoid smoking, eating food, coffee or other drinks (drinking water is allowed) at least 3 h before the test. The biosensor is worn on the index finger (second finger) and bind the cuff of the non-habitual hand to block the blood flow. Tentatively, the RHI < 1.67 is regarded as endothelial dysfunction. At present, there is no study on the normal reference value of RHI, and our study will also preliminarily establish the normal range of RHI in Chinese population.

#### Arterial stiffness by brachial-ankle artery pulse wave velocity (ba-PWV) examination

Ba-PWV is examined by automatic detection equipment for arterial function (MB-3000, China). Keep the room temperature at about 22–25 °C in the examination room. The examinee should rest for at least 5 min before the measurement; rest for about 20 min after any exercise before starting the measurement. Install cuff on both arms and ankles, left upper arm (yellow), right upper arm (red), left ankle (green), right ankle (black). The air duct orifice of the upper arm cuff is placed on the same axis as the brachial artery of the upper arm, and the lower edge of the cuff is 2 to 3 cm, from the elbow fossa so that the upper and lower edges can only enter one finger. Extend the air hose on the ankle cuff upward along the medial side of the ankle. The lower edge of the lower limb cuff is 1 to 2 cm horizontally away from the medial malleolus. Place electrocardiogram (ECG) electrodes on the left and right wrist. Place the heart sound sensor at the second rib level of the right edge of the sternum or the third rib level in the middle of the sternum or the fourth rib level of the left edge of the sternum. Enter the examinee's information, click the start button when each waveform is stable, and the machine will automatically analyze the results. Age and sex adjusted ba-PWV values are used to define arteriosclerosis.

#### Cardio-ankle vascular index (CAVI) evaluation

CAVI is examined by vascular equipment (VS-1500, Fukuda, Japan). Cuff, heart sound sensor and ECG electrode are placed in the same way as  ba-PWV. After observing that the waveform on the screen is stable, press the start key to start the measurement. After hearing the deflation sound, there should be six (+) signs on the screen, two in each row. Some of the examined blood vessels have severe hardening or stenosis, and there should be at least three (+) signs, one in each row. Confirm that the CAVI self-test result is "+" or "+". If it is "−" or "−", please reconfirm that the ECG electrodes, cuffs and heart sound sensors are connected correctly. CAVI > 9 on either side will be defined as arteriosclerosis.

#### Ankle–branchial index (ABI)

When detecting CAVI and ba-PWV, the value of ABI will be detected respectively. In this study, we will analyze the differences between the two kinds of ABI.

#### Carotid ultrasound detection

Carotid intima-media thickness (CIMT) and plaque are assessed with ultrasound (VIVID E80, GE, USA) with a connected electrocardiogram. The whole extracranial carotid artery was scanned by longitudinal and cross-sectional two-dimensional (2D) B-mode image, including common carotid artery, bifurcation of common carotid artery (CCA), extracranial segment of internal carotid artery (ICA) and extracranial segment of extracranial carotid artery (ECA) according to the Mannheim Carotid Intima-Media Thickness and Plaque Consensus [13].

CIMT is a double-line pattern visualized by echography on both walls of the CCA in a longitudinal image. Two parallel lines, which consist of the leading edges of two anatomical boundaries, form it: the lumen-intima and media-adventitia interfaces [13]. Edge detection system is used for semi-automatic measurements performed on a 10-mm segment of CCA instantaneously. Using the semi-automatic measurement software, the sampling frame was sampled at 1 cm in two-dimensional mode and measured the posterior wall at the bifurcation of the common carotid artery and 1 cm from the bifurcation of the common carotid artery. Measurement of CIMT should occur within a region free of plaque with a clearly identified double-line pattern in diastole on the selected frame. The measurement parameters include the average value of CIMT, the maximum value of CIMT, the minimum value of CIMT, the standard deviation of CIMT and the number of successful CIMT measurements. CIMT ≥ 1.0 mm is defined as thickening.

Plaques are focal structures encroaching into the arterial lumen of at least 0.5 mm or 50% of the surrounding CIMT value or demonstrates a thickness > 1.5 mm as measured from the intima-lumen interface to the media-adventitia interface from 2 different angles, in longitudinal and cross-sectional views [13].

The evaluation of carotid stenosis will be combined with the results of vascular diameter and area measurement and hemodynamic parameters. A peak systolic velocity (PSV) of less than 125 cm/s corresponds to lower than 50% stenosis; of 125–230 cm/s corresponds to 50–69% stenosis; and more than 230 cm/s corresponds to greater than 70% stenosis [14, 15]. The intravascular diameter method was used to evaluate the carotid stenosis using the European Carotid Surgery Trial (ECST), that is, the ratio of the residual diameter of the stenosis to the original diameter of the stenosis. The area method evaluates the stenosis rate as the area stenosis rate = [1 − (minimum lumen cross-sectional area/original lumen cross-sectional area)] × 100%.

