### Beijing Vascular Health Stratification (BVHS) (see Fig. 2)

**Fig. 2 Fig2:**
[figure not shown]
Beijing vascular health stratification (BVHS). FMD, Flow mediated vasodilation; RHI, Reactive hyperemia index; CF-PWV, Carotid-femoral artery pulse wave velocity; CAVI, Cardio-ankle vascular index

BVHS is a system to evaluate vascular health by a serious of vascular indicators, including endothelial function, arterial stiffness, atherosclerotic plaque and vascular stenosis. The standard of BVHS is showed in Fig. 2.

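### Carotid stenosis by the diameter method is worded as the open fraction of the lumen, opposite in direction to the area formula and velocity bands beside it

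*Protocol article*

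**What the plan says.** The protocol article describes three ways of assessing carotid stenosis under Carotid ultrasound detection, and says how they are used: "The evaluation of carotid stenosis will be combined with the results of vascular diameter and area measurement and hemodynamic parameters".

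- **Velocity.** PSV is mapped to percentage stenosis in three rising bands: under 125 cm/s is below 50%, 125–230 cm/s is 50–69%, and for the top band "more than 230 cm/s corresponds to greater than 70% stenosis".
- **Diameter.** "The intravascular diameter method was used to evaluate the carotid stenosis using the European Carotid Surgery Trial (ECST"), which the article then explains as "the ratio of the residual diameter of the stenosis to the original diameter of the stenosis".
- **Area.** The next sentence gives "area stenosis rate = [1 − (minimum lumen cross-sectional area/original lumen cross-sectional area)] × 100" (as a percentage).

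The section on the BVHS lists the system's components as "including endothelial function, arterial stiffness, atherosclerotic plaque and vascular stenosis". The grading standard itself is in Fig. 2, which is not shown. The Sample size calculation section makes the BVHS grade the exposure of the cohort. Table 1 schedules carotid ultrasound at baseline only, and the Results section reports 1648 participants enrolled.

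**The concern.** A stenosis percentage should be 0 for an unobstructed vessel and 100 for an occluded one. Residual diameter divided by original diameter behaves the other way round: it measures how much of the lumen remains. The area formula has the subtraction from 1 and the diameter definition does not, although both are offered as measures of the same thing and are to be used together.

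This is not detail that a condensed article leaves to a fuller document. The article does give a definition, and that definition runs opposite to the two statements on either side of it.

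The risk is practical. Someone who programs the derivation, completes the case record form or reanalyses the data from the published text would obtain a diameter value that falls as disease worsens. Because stenosis feeds the BVHS grade, a reversed input could place participants in the wrong grade. The schedule has no repeat carotid scan that might expose such an error later.

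**Working it through.** The article states no numerical result on this point, so there is no figure to reproduce. The check compares the three statements in one paragraph for direction and size.

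**Inputs**, all from Carotid ultrasound detection:
- diameter method as worded: value = r, where r = residual diameter / original diameter;
- area method as worded: value = 1 − (minimum area / original area);
- PSV bands: higher velocity means a higher percentage.

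**Assumption, used only for the area column:** the lumen is circular, so the area ratio is r² and area stenosis is 1 − r². The article does not state this. The direction of the comparison does not depend on it, since the area ratio falls as the lumen narrows whatever its shape.

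**Formulas:** as worded, 100 × r; complement, 100 × (1 − r); area, 100 × (1 − r²).

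| r | Diameter method as worded | Complement, 1 − r | Article's area formula (circular lumen) |
|---|---|---|---|
| 1.0 (open) | 100% | 0% | 0% |
| 0.9 | 90% | 10% | 19% |
| 0.7 | 70% | 30% | 51% |
| 0.5 | 50% | 50% | 75% |
| 0.3 | 30% | 70% | 91% |
| 0.1 | 10% | 90% | 99% |
| 0 (occluded) | 0% | 100% | 100% |

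Example at r = 0.3: as worded 100 × 0.3 = 30%; complement 100 × (1 − 0.3) = 70%; area 100 × (1 − 0.09) = 91%.

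**Reading the table**
1. At the two ends, the worded diameter rule gives 100% for an open vessel and 0% for an occluded one. The article's own area formula gives 0% and 100%.
2. Between the ends, the worded value falls as narrowing increases, while the complement, the area value and the PSV bands all rise.
3. The worded value equals its complement only where r = 1 − r, that is, at r = 0.5. Elsewhere the error is |r − (1 − r)| = |2r − 1|: 40 percentage points at r = 0.3 (|0.6 − 1| = 0.4) and 80 at r = 0.9 (|1.8 − 1| = 0.8).

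The contradiction is therefore visible within the paragraph, without any outside source on the named method.

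**The case against.** The strongest reply is that this is a slip of wording. The article names an established method and then glosses it loosely in words; it does not set out a computing formula. The area formula and the PSV bands make the intended direction clear, and a literal reading has the absurd result that a healthy artery is fully stenosed. Nothing in the article shows that any value was computed the wrong way round. This stands as a reason for restraint about consequences. It does not rescue the sentence, which is wrong as it reads.

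Three stronger readings are tempting, and the documents do not support them.

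- **That the whole stenosis component of BVHS is inverted, and the association between BVHS and major adverse cardiovascular events (MACEs) biased.** Diameter is one of three inputs that are combined. Reversing it would set it against the other two; it need not reverse the combined judgement. How the grade is formed is in Fig. 2, which is not shown.
- **That participants swap sides of a 50% cut-point.** In the text, 50% is a boundary of the velocity mapping, and the Discussion uses it to describe advanced carotid disease. Nothing visible says that BVHS grades on 50%, or that the diameter percentage decides the grade.
- **That diameter and area percentages are read on one scale.** The two differ, as the table shows, but the article labels the area result separately and nowhere tells anyone to apply an area value to a diameter threshold. How discordant measures are resolved is detail that an article may leave to the full protocol.

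It can also be said that few participants would be affected. The only frequency in the article is the Discussion's global estimate for carotid stenosis at ages 30–79, 1.5% (1.1–2.1%). If it applied here, which is an assumption, that is 1648 × 0.015 ≈ 25 people (1648 × 0.011 ≈ 18 to 1648 × 0.021 ≈ 35). This does not settle the matter: the article does not say in whom the diameter ratio is recorded, and mildly narrowed vessels would show the larger errors under the literal rule.

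**Conclusion.** The point holds as an error in a stated measurement definition. Residual over original diameter is the complement of stenosis, and it contradicts the area formula and the direction of the PSV bands in the same paragraph. Followed literally, it reverses the diameter reading, with an error of |2r − 1| that vanishes only at r = 0.5. That conclusion rests on the article's own text; the circular-lumen assumption affects only the size of the area figures.

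The effect on BVHS grades is possible but cannot be sized. It depends on whether values were actually derived as worded, on how the three measures are combined, and on grading rules that are not shown. Misgrading is therefore a risk to be excluded by a check, not an established result, and no claim about bias in the BVHS–MACE association follows. The correction is worth making because the sentence gives a wrong value to anyone who follows it.

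**What to change.** Replace the verbal gloss on the diameter method with a definition in the same form as the area formula:

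**diameter stenosis (%) = [1 − (residual lumen diameter / original lumen diameter)] × 100%**

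Then check that the baseline values already recorded were derived this way. Useful signals are diameter percentages that run against the area value or the PSV band for the same vessel. If any were entered as the open fraction, they can be recovered as 100 minus the recorded value, provided it is known which records are affected; where the two diameters were stored, the percentage can be recomputed from them.

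The cost is one corrected sentence and a derivation check in the data capture system. No new scan is needed, and the sample size and analysis methods are unaffected.

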### Beijing Vascular Health Stratification (BVHS) (see Fig. 2)

**Fig. 2 Fig2:**
[figure not shown]
Beijing vascular health stratification (BVHS). FMD, Flow mediated vasodilation; RHI, Reactive hyperemia index; CF-PWV, Carotid-femoral artery pulse wave velocity; CAVI, Cardio-ankle vascular index

BVHS is a system to evaluate vascular health by a serious of vascular indicators, including endothelial function, arterial stiffness, atherosclerotic plaque and vascular stenosis. The standard of BVHS is showed in Fig. 2.

### End points and assessment

The primary outcome will be the incidence of MACEs.

MACEs include all cause death, cardiovascular death, non-cardiovascular death, undetermined cause of death, myocardial infarction (MI), hospitalization for unstable angina (UA), transient ischemic attack (TIA) and stroke, heart failure (HF) event, percutaneous coronary intervention (PCI), coronary artery bypass grafting (CABG), peripheral vascular intervention (PVI), stent thrombosis [16].

Cardiovascular death includes acute MI, sudden cardiac death, heart failure, stroke, cardiovascular procedure and cardiovascular hemorrhage etc.

Definition of MI is clinical syndrome where there is evidence of myocardial necrosis in a clinical setting consistent with acute myocardial ischemia, including presence of acute symptoms of myocardial ischemia, such as chest, upper extremity, mandibular, or epigastric discomfort, or an ischemic equivalent such as dyspnea or fatigue; presence of new or presumed new significant ST-segment-T wave (ST-T) changes or new left bundle-branch block (LBBB) consistent with acute myocardial ischemia; presence of new or presumed new pathological Q waves consistent with MI; presence of thrombus in a major epicardial vessel consistent with an acute MI; demonstration of a new change in myocardial viability or function consistent with MI; occurrence of an adverse angiographic finding during PCI consistent with acute myocardial ischemia; angiographic documentation of a new CABG or new native coronary artery occlusion within 48 h of CABG surgery; cardiac biomarker level [16].

Definition of hospitalization for UA include unscheduled hospitalization for the management of UA, occurring within 24 h of the most recent symptoms. Hospitalization is defined as an admission to an inpatient unit or a visit to an emergency department (ED) that results in at least a 24-h stay (or a change in calendar date if the hospital admission or discharge times are not available) [16].

Stroke is defined as an acute episode of focal or global neurological dysfunction caused by brain, spinal cord, or retinal vascular injury as a result of hemorrhage or infarction. Categorical description of stroke type classified into 1 of 3 mutually exclusive categories (ischemic, hemorrhagic, undetermined) [16].

TIA is defined as transient episode of focal caused by brain, spinal cord, or retinal ischemia without acute infarction [16].

HF event is defined as presentation of the patient for an urgent, unscheduled clinic/office/ED visit or hospital admission, with a primary diagnosis of HF, where the patient exhibits new or worsening symptoms of HF on presentation, has objective evidence of new or worsening HF, and receives initiation or intensification of treatment specifically for HF [16].

PCI is the placement of an angioplasty guidewire, balloon, or other device (e.g. stent, atherectomy, brachytherapy, or thrombectomy catheter) into a native coronary artery or CABG for the purpose of mechanical coronary revascularization [16].

CABG surgery is a procedure performed to bypass partially or completely occluded coronary arteries with veins and/or arteries harvested from elsewhere in the body, thereby improving the blood supply to the coronary circulation supplying the myocardium (heart muscle) [16].

A PVI is a catheter-based or open surgical procedure designed to improve arterial or venous blood flow or otherwise modify or revise vascular conduits. Procedures may include, but are not limited to, percutaneous transluminal balloon angioplasty, stent placement, thrombectomy, embolectomy, atherectomy, dissection repair, aneurysm exclusion, treatment of dialysis conduits, placement of various devices, intravascular thrombolysis or other pharmacotherapies, and open surgical bypass or revision [16].

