**Method:**

Beijing vascular health stratification (BVHS) is an evaluation system aiming at vascular health, combined the endothelial function, arteriosclerosis, atherosclerotic plaque and vascular lumen stenosis to comprehensively assess the vascular health and grade it. This study will explore the predictive value of the combined evaluation of vascular structure and function for cardiovascular events and assess the predictive value of BVHS and compare it with the existing risk assessment systems. A total of 1500 subjects will be enrolled into the prospective cohort study from a community and will be followed up for at least 3 years from July 1, 2020 to June 30, 2023. Subjects aged 40 or above, without coronary heart disease, stroke or peripheral artery disease, with written informed consent will be included; subjects with end-stage hepatorenal diseases (uremia, renal failure, cirrhosis, liver failure), mental disorders or cognitive disorders, with any other factors that the researcher thinks are not suitable for the study will be excluded. Traditional cardiovascular risk factors will be collected as adjusted confounders.

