## Background

Vascular health indicators, including lumen stenosis and dysfunction, both reflect the long-term cumulative effects of traditional and unidentified cardiovascular (CV) risk factors before and after clinical vascular events, and can be regarded as an alternative end point indexes for target organ damage and risk prediction [1]. Several markers have been considered as the reflection of vascular health, among them endothelial function, arterial stiffness and carotid atherosclerosis are the most common indicators [1]. Endothelial dysfunction may represent the effect of traditional CV risk factors on vascular health [2]. Arterial stiffness is increasingly recognized as a surrogate end point for cardiovascular disease (CVD) and as a risk factor for clinical hypertension [3, 4]. Carotid ultrasound measurement of intima-media thickness (IMT) along with carotid plaque are emerging as the focus of carotid artery ultrasound imaging for CV risk prediction [5]. Currently, studies on assessing vascular health use only one or more of these indicators [6–8]. Beijing Vascular Health Stratification (BVHS) was put forward to assess vascular health including all stages of vascular disease progression, from endothelial function to arteriosclerosis to vascular stenosis [9]. BVHS is a risk prediction tool using subclinical vascular measures such as endothelial function, arterial stiffness, carotid atherosclerotic plaques and artery stenosis by non-invasive detections. Furthermore, traditional risk factors are not included in BVHS, but are used as adjusted confounding factors to analyze the independent predictive role of BVHS.

All the markers are graded as artery functional injury or structural disease or both. Our previous retrospective study found that the BVHS was a comprehensive risk assessment system and was independent of traditional CV risk factors [10]. However, the previous study did not develop a strict study design and follow-up plan. Therefore, this study was designed as a prospective cohort study to verify the previous research results and further explore the clinical value of BVHS for the prediction of major adverse cardiovascular events (MACEs).

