### Incidence of end point events

The endpoint events concerned in this study are MACEs, the most important of which are coronary heart disease, stroke and related death. In previous studies, the standardized annual incidence of coronary heart disease in people over 45 years old in Beijing was estimated to be 497/100,000 [17], and the standardized annual incidence of stroke in people over 40 years old in China was estimated to be 533/100,000 [18]. Regardless of the difference in age composition of the population, during the 3-year follow-up period of this study, the incidence of CV events was estimated to be about 30/1000 people, and a total of about 45 cases of CV events could be obtained.

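### Primary MACE counts any peripheral vascular intervention, so elective treatment of a stenosis already graded by BVHS at baseline is scored as a predicted event

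*Protocol article*

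**What the plan says.** **Predictor.** The section on Beijing Vascular Health Stratification describes a grading built from several indicators, "including endothelial function, arterial stiffness, atherosclerotic plaque and vascular stenosis". The Abstract lists the same four elements. The Background presents the scale as "including all stages of vascular disease progression, from endothelial function to arteriosclerosis to vascular stenosis", which puts stenosis at the end of the sequence. Carotid ultrasound detection sets out how stenosis is graded, up to the band where "more than 230 cm/s corresponds to greater than 70% stenosis". Table 1 (Follow up) schedules carotid ultrasound at baseline only.

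**Outcome.** End points and assessment makes MACE incidence the primary outcome and includes among its components "percutaneous coronary intervention (PCI), coronary artery bypass grafting (CABG), peripheral vascular intervention (PVI), stent thrombosis". The definition begins "A PVI is a catheter-based or open surgical procedure designed to improve arterial or venous blood flow". It goes on to name stent placement, atherectomy and open bypass among the examples, with no requirement that the procedure be unplanned, symptom-driven or on a new lesion.

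**Possible safeguards.** Entry excludes coronary heart disease, stroke and peripheral artery disease, but no criterion names asymptomatic carotid stenosis. The Follow up section has an adjudication committee review all events and confirm the diagnosis. It gives no rule for procedures on a lesion already seen at baseline.

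**The concern.** The graded lesion and the counted event can be one and the same. If a participant's baseline scan shows a carotid stenosis and it is later stented or operated on electively, the printed definition is met. The event falls in someone whose grade is high because of that stenosis. It says nothing about whether BVHS foretells infarction, stroke or death.

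This is not random misclassification. A procedure on a graded stenosis can occur only in a person graded for it, so the error runs one way: it raises the Cox hazard ratio and the C statistic for BVHS. The second aim, comparison with China-PAR and the Pooled Cohort Equations, tilts the same way. The Discussion says most existing models rest on traditional risk factors, and such a model gains less from events that a stenosis finding triggers. Independent prediction and this comparison are the study's two stated questions, so a one-directional error in the endpoint deserves attention even if it is small.

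**Working it through.** **1. The plan's own event count.** Incidence of end point events gives 497 (coronary heart disease) and 533 (stroke) per 100,000 per year. 497 + 533 = 1030; × 3 years = 3090 per 100,000, or 30.9 per 1000. The article rounds this to 30 per 1000, and 1500 × 0.030 = 45, matching "a total of about 45 cases of CV events could be obtained". This count holds coronary disease and stroke only. It contains no PVI, and it omits other MACE components such as non-cardiovascular death, heart failure and TIA.

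**2. Base for the calculation.** Sample size calculation splits at the median BVHS, sets the incidence in the lower half at 0.03, and takes a risk ratio of 1.94, so p1 = 0.03 × 1.94 = 0.0582. With 750 people per half:
- lower half: 750 × 0.03 = 22.5 events
- upper half: 750 × 0.0582 = 43.65 events
- ratio: 43.65 / 22.5 = 1.94

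Each additional upper-half event adds 1 / 22.5 = 0.044 to the risk ratio.

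**3. Number of extra PVIs (assumed).** The Discussion quotes a carotid stenosis prevalence of 1.5% (1.1–2.1%). That is a global figure for ages 30–79, so applying it here is an assumption. The share treated is not in the article; 5–30% is assumed. Then k = 1500 × prevalence × share treated. At 1.5% there are 22.5 people with stenosis, all taken to lie in the upper half.

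**4. Result, (43.65 + k) / 22.5, at 1.5% prevalence:**
- 5% treated: k = 1.125, ratio 1.99
- 10%: k = 2.25, ratio 2.04
- 20%: k = 4.5, ratio 2.14
- 30%: k = 6.75, ratio 2.24

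Extremes of prevalence: 1.1% with 5% treated gives k = 0.825 and ratio 1.98; 2.1% with 30% gives k = 9.45 and ratio 2.36.

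**5. If BVHS predicted nothing else.** With 22.5 events in each half, (22.5 + k) / 22.5 runs from 1.05 (k = 1.125) to 1.30 (k = 6.75).

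**6. Dilution.** The base in step 2 rests on the coronary-plus-stroke incidence. Counting the other MACE components enlarges the lower-half total and shrinks each increment. For example, if they doubled it to 45 (an assumption), each PVI would add 1 / 45 = 0.022. Treated people who would have had another MACE anyway also add less. The figures in steps 4 and 5 are therefore upper values for the stated prevalence and treated share.

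**The case against.** The strongest reply is that the mechanism is conjectural. Nothing in the article says that a baseline scan leads to a procedure. Where the Discussion turns to management, it speaks of advice tailored to vascular results, education, lifestyle and drug therapy, not revascularisation. The treated share is assumed, and at its low end the effect is negligible. This stands as a limit on size. It does not remove the overlap, which follows from the printed definitions.

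It can also be said that handling of elective procedures belongs in an adjudication charter. That would hold if the article were silent, but it prints the definition, and a committee applying it would confirm such a procedure, not reject it.

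The contrast with neighbouring components is weaker than it looks. The article does write "Definition of hospitalization for UA include unscheduled hospitalization for the management of UA" and asks for an urgent, unscheduled visit or an admission with new or worsening symptoms for heart failure. Those are clinical syndromes, however. PCI and CABG are the like-for-like components, and they carry no urgency limit either. A reader might infer that the same circularity affects PCI and CABG. The article does not support that, because BVHS as described does not image the coronary arteries.

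Finally, dropping PVI from the composite altogether would discard genuine new events such as later limb revascularisation. That objection is sound, and it points to a narrower remedy.

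**Conclusion.** The overlap is real and its direction is certain; its size is unknown and probably small. On the plan's own inputs each such PVI adds about 0.044 to the risk ratio. A prevalence of 1.5% and a treated share of 5–30%, both assumed, move 1.94 to about 1.99–2.24, and less with the full MACE list in the base.

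Two stronger readings should be resisted. A reader might take the 45 events as the whole endpoint and split them at 1.94, giving 45 / 2.94 = 15.3 in the lower half and 1 / 15.3 = 0.065 per PVI. But the 45 cover coronary disease and stroke only, and the sample-size section assigns 0.03 to the lower group, not to the whole cohort. A reader might also put a number on the gain in the C statistic. That needs the grade boundaries in Fig. 2, which was not available here, so only the direction can be stated.

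The conclusion assumes that people with stenosis fall in the higher half of BVHS. The Background's ordering supports this, but the exact cut-offs were not seen. The change is worth making because it costs very little, not because the bias is shown to be large.

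**What to change.** In End points and assessment, add to the PVI definition that a PVI counts towards the primary MACE only when the adjudication committee finds that it treated new symptoms or a site not recorded as stenosed at the baseline carotid ultrasound. Report the remaining PVIs separately by BVHS grade. As a sensitivity analysis, repeat the BVHS hazard ratio, the C statistic and the comparison with China-PAR and the Pooled Cohort Equations with all PVI excluded.

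The cost is one more item for adjudication and a slightly narrower composite. No new measurements are needed, since the baseline ultrasound and the committee are already planned. No event in the planned 45 is lost, because that count never included PVI.
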